***Secondary outcomes***

Secondary research goals include an exploration of :

- Percentage of patients in each group that after 12 month achieve one or more of the following targets: HbA1c <6.5% or HbA1c reduction >0.5%; total cholesterol <175 mg/dl; LDL cholesterol <100 mg/dl; HDL cholesterol >40 mg/dl; triglycerides <150 mg/dl; systolic blood pressure (BP) <130 mmHg; diastolic BP <80 mmHg; BMI reduction >1; waist circumference reduction >5 cm.
- Difference between groups in terms of reduction of HbA1c, serum triglyceride and LDL-cholesterol, systolic and diastolic BP, BMI and waist circumference and increment of serum HDL-cholesterol.
- Difference between groups in terms of reduction of number and/or dosage of glucose-, lipid- and BP-lowering drugs.
- Difference between groups in terms of reduction of global cardiovascular 10-year risk (UKPDS risk engine tables).
- Difference between groups in terms of improvement of well-being.
- Difference between groups in terms of direct medical costs and direct and indirect social costs.
- Dose/response relationship between the quality (volume and intensity) of exercise training and modifiable cardiovascular risk factors.
- Relationship between physical fitness at baseline and during the study and modifiable cardiovascular risk factors.

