# ***Eligibility criteria***

# The inclusion and exclusion criteria are summarized in Table 1. The main entry criterion is known type 2 diabetes plus >2 other MS traits, as defined according to the IDF criteria [16], i.e. waist circumference M >94 cm F >80 cm; triglycerides >150 mg/dl and/or HDL cholesterol M <40 mg/dl F <50 mg/dl or specific treatment; and BP >130/85 mmHg or specific treatment. Additional requirements are age from 45 to 75 years, duration of diabetes > 1 year, BMI 27-40 kg/m2, sedentary lifestyle for at least six months, ability to walk without assistance and eligibility after cardiovascular evaluation. Patients having any condition that limits or contraindicates the exercise will be excluded from the study.

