# On the third visit (R3), basal anthropometric and blood pressure (BP) measurements will be obtained and registered in the database, together with results of laboratory tests performed centrally. Subsequently all patients will receive a treatment regimen aimed at achieving optimal glycemic, lipid, BP and body weight targets, as established by current guidelines. This program will eventually include glucose-, lipid- and BP-lowering agents as needed and, when indicated, anti-platelet drugs. For ethical reasons, drugs will be also adjusted throughout the study to attain target levels and to account for reduced needs. The treatment regimen will include also a dietary prescription, which will be preceded by a preliminary nutritional evaluation with assessment of BMI and the individual patient requirements and preferences. The diet will contain 55% calories from complex carbohydrates, 30% from fat, and 15% from protein. Since all patients are overweight or obese, they will receive a low calorie diet (negative balance of 500 kcal/day, not <1500 Kcal in males and 1200 Kcal in females), calculated by adding the estimated energy expenditure from non-conditioning or non-volunteer and conditioning or volunteer physical activity to basal metabolism estimated using the gas exchange analyzer FitMate (Cosmed, Rome, Italy). Baseline LTPA will be calculated by multiplying the weekly hours spent in the various activities, as reported in the Minnesota LTPA questionnaire, by the metabolic equivalent (MET) score of each activity, and expressed as METs· h–1 · week–1. Patients will be also given a diary to be filled in daily with type of physical activity performed and time spent in each of them (Figure 2 and Table 4). Finally, patients will receive a list of intermediate, group B biochemical measurements, to be performed at each center laboratory immediately before the next visit (Table 3), will be prescribed.

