***Statistical analysis plan***

The c2 test for categorical variables and the Student’s t test or the corresponding nonparametric Mann-Whitney test for continuous variables will be utilized to compare patients’ characteristics at baseline. The efficacy of intervention on primary and secondary endpoints will be assessed using the unpaired t-test or the Mann Whitney U test for continuous variables, by comparing between-groups changes from baseline to end-of-study. For categorical variables (i.e. medications), logistic regression analysis will be applied, with end-of-study rate of use included in the model as the dependent variable and baseline rate of use and study arm included as covariates.

To account for change in medication throughout the 12-month period, multiple regression analysis will be performed, with baseline-to-end-of-study changes as dependent variable and treatment at baseline and treatment initiation during the study as dichotomous variables (yes versus no), whereas drug dosage will not be taken into consideration.

Within group end-of-study vs. baseline values will be compared using the McNemar test for categorical variables and the Wilcoxon signed ranks test for continuous variables. To identify independent predictors of HbA1c changes from baseline, a multiple regression analysis was applied, with mean value of METs, baseline HbA1c values, gender, age, and changes in HOMA-IR, BMI, waist, total, LDL-cholesterol and HDL-cholesterol, and hs-CRP as covariates forced in the model.

Multivariate analysis techniques (multiple or logistic regression) will be used to adjust for differences in the distribution of one or more parameters between the two arms, whereas the ANOVA trend test will be applied for evaluating the relationship of volume and intensity of exercise training (dose/response) and fitness variation with modifiable cardiovascular risk factors.

The likelihood to achieve glycaemic and nonglycaemic targets after 12 months will be estimated using logistic regression, adjusted for baseline status (on-target vs. not-on-target).

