| **F2** | Intermediate anthropometric and blood pressure measurements  Registration of results of intermediate, group B biochemical measurements (with eventual treatment regimen modification)  Registration of data from the diary of physical activity  Structured individualized counseling reinforcement  Prescription for intermediate, group B biochemical measurements |
| **F3** | Intermediate anthropometric and blood pressure measurements  Registration of results of intermediate, group B biochemical measurements (with eventual treatment regimen modification)  Registration of data from the diary of physical activity  Structured individualized counseling reinforcement |
| **F4** | Final anthropometric and blood pressure measurements  Collection of blood and urine samples for baseline, Group A biochemical measurements and forwarding to the central laboratory via express courier  Registration of data from the diary of physical activity  Administration of the SF-36 and the WHO-DTSQ questionnaires  Appointment at the Metabolic Fitness Center for metabolic fitness assessment and strength evaluation |

**Table 3:** Biochemical measurements

***Group A*** – to be performed at central laboratory (Laboratory of Clinical Chemistry, Sant’Andrea Hospital, Rome, Italy) at baseline and at the end of the study.

- HbA1c a, blood glucose b, C-peptide, and insulin levels c with calculation of the Homeostasis Model Assessment-Insulin Resistance (HOMA-IR) index from fasting glucose and insulin levels using the HOMA Calculator© software ([www.dtu.ox.ac.uk/homa/index.php](http://www.dtu.ox.ac.uk/homa/index.php));
- serum triglycerides and total and HDL-cholesterol levels b with LDL-cholesterol calculation using the formula: total cholesterol – [HDL-cholesterol + (triglycerides/5)];
- BUN, uric acid and serum creatinine b, with calculation of estimated glomerular filtration rate (eGFR) is calculated from serum creatinine by the modified Modification of Diet in Renal Disease Study Group equation ([www.kidney.org/professionals/KDOQI/gfr_calculator.cfm](http://www.kidney.org/professionals/KDOQI/gfr_calculator.cfm)), and urinary albumin d / creatinine b ratio in spot urine sample (these data are presented elsewhere);
- serum aspartate aminotransferase, alanine aminotransferase, -glutamyl-transpeptidase and creatine phosphokinase levels b;
- hs-C reactive protein b.

a High-performance liquid chromatography (Adams TMA1C HA-8160, Menarini Diagnostics, Florence, Italy).

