b VITROS 5,1 FS Chemistry System (Ortho-Clinical Diagnostics, Inc, Raritan, NJ, USA)

c Chemiluminiscent immunometric assays (Immulite 2000 Thes; Diagnostic Products Corporation, Los Angeles, CA, USA)

dmAlb VITROS (Ortho-Clinical Diagnostics, Inc)

***Group B***– to be performed in each centre laboratory at 3, 6 an 9 months.

- HbA1c and blood glucose levels;
- serum triglycerides and total and HDL cholesterol levels with LDL cholesterol calculation;
- BUN, serum creatinine, urinalysis, uric acid (if present hypeuricemia);
- serum aspartate aminotransferase, alanine aminotransferase, -glutamyl-transpeptidase and creatine phosphokinase levels (if treated with statins);
- plasma sodium and potassium levels (if treated with BP-lowering agents).

**Table 4:** List of Physical Activities (in Italian) and the relative METs intensities utilized to predict the accumulated volume of physical activity (METs·h-1·wk-1). Activities included and corresponding METS values are derived from the Minnesota Leisure Time Physical Activity Questionnaire.

| **PHYSICAL ACTIVITY** | **METS** |
| --- | --- |

1 Passeggiare 3.5

2 Camminare da casa al lavoro o nella pausa lavoro 4.0

3 Camminare (portando un carrello con la spesa) 3.5

4 Camminare (portando le sporte della spesa) 5.5

5 Salire le scale 8.0

6 Camminare in campagna/traking 6.07

7 Escursioni con lo zaino 7.0

8 Scalate in montagna 8.0

9 Andare in bicicletta al lavoro 4.0

10 Ballo 4.5

11 Aerobica o balletto 6.0

12 Giocare con i bambini 4.5

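### Table 3 applies the triglycerides/5 formula for LDL to every patient without a triglyceride limit, so very high triglycerides yield impossible LDL values that count as reaching the LDL target (minor; secondary outcomes only)

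*Protocol*

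**What the plan says.** Protocol Table 3, Group A (central laboratory, baseline and end of study), prescribes "LDL-cholesterol calculation using the formula: total cholesterol – [HDL-cholesterol + (triglycerides/5" with the brackets then closed. No range of validity, alternative assay or missing-value rule is attached. Table 3, Group B (centre laboratories at 3, 6 and 9 months) lists "serum triglycerides and total and HDL cholesterol levels with LDL cholesterol calculation", again without a limit.

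Under Eligibility criteria the main entry condition is "known type 2 diabetes plus >2 other MS traits". The lipid trait is "triglycerides >150 mg/dl and/or HDL cholesterol M <40 mg/dl F <50 mg/dl or specific treatment", which gives triglycerides a lower bound only. Neither list in Table 1 contains an upper bound.

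Calculated LDL is used in three places:
- the 12-month target "LDL cholesterol <100 mg/dl" (Secondary outcomes);
- the between-group comparison of "reduction of HbA1c, serum triglyceride and LDL-cholesterol" (Secondary outcomes);
- the regression for predictors of HbA1c change, where LDL change is a covariate (Statistical analysis plan section).

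The target analysis is a logistic regression "adjusted for baseline status (on-target vs. not-on-target").

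**The concern.** The formula replaces the cholesterol carried by triglyceride-rich particles with a fixed fraction of triglycerides. Nothing in it stops the subtraction from exceeding what is available, so a high enough triglyceride value drives calculated LDL to zero or below. The protocol would score that patient as an LDL success and carry the number into the change analysis. The baseline on-target covariate would be misclassified in the same way.

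The population makes this more than a curiosity. It is a metabolic-syndrome population, and raised triglycerides are one of several ways to meet the lipid trait.

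The error could also differ by arm. A larger triglyceride reduction in EXE is one of the effects the trial looks for. If it occurs, the understatement of LDL shrinks more in EXE than in CON, which makes EXE look worse on LDL. Baseline blood is drawn at visit R2, before the treatment regimen is prescribed at R3. A triglyceride fall in both arms would therefore also distort within-group LDL change.

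**Working it through.** **Inputs.** From the protocol: LDL = TC − (HDL + TG/5) (Table 3); target LDL <100 mg/dl (Secondary outcomes); 600 recruited (Sample size calculation). Assumed, because the documents give no lipid distribution: HDL 40 mg/dl, illustrative TC and TG values, a true ratio TG/k, and a log-normal triglyceride distribution.

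**1. The plan's own figure.** The protocol gives no figure for LDL. Its one design figure concerns HbA1c and is reproduced: 2 × (1.6 × (1.96 + 1.2816)/0.5)² = 215.2, against the stated 215 per arm. LDL plays no part in it.

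**2. What the formula returns (HDL 40, mg/dl).**

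| TC | TG 400 | TG 600 | TG 800 | TG 1000 |
|---|---|---|---|---|
| 200 | 80 | 40 | 0 | −40 |
| 240 | 120 | 80 | 40 | 0 |

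For example, 200 − (40 + 1000/5) = −40. LDL turns negative once TG exceeds 5 × (TC − 40), which is 675, 800, 1000 or 1200 for TC 175, 200, 240 or 280. All zero or negative results satisfy LDL <100.

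**3. Size of the error.** Suppose the cholesterol in triglyceride-rich particles is really TG/k. Then calculated minus true LDL = TG/k − TG/5.

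| Assumed k | TG 150 | TG 400 | TG 800 |
|---|---|---|---|
| 5 | 0 | 0 | 0 |
| 6 | −5 | −13 | −27 |
| 8 | −11 | −30 | −60 |
| 10 | −15 | −40 | −80 |

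At TG 800 a true LDL of up to about 127, 160 or 180 mg/dl (100 plus the error for k = 6, 8 or 10) would be scored as on target.

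**4. Movement with treatment.** Hold true LDL at 120. Let TG fall from 800 to 400, with k moving from 8 to 6.
- Before: 120 + 800/8 − 800/5 = 60.
- After: 120 + 400/6 − 400/5 = 106.7.

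Calculated LDL rises by 46.7 mg/dl and the patient leaves the target range with no true change.

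**5. How many patients.** P(TG > 400) under assumed log-normal distributions is 1.8% (median 140, log-SD 0.50), 3.3% (160, 0.50), 4.8% (160, 0.55) and 7.3% (180, 0.55). Of 600 patients that is about 11 (0.018 × 600) to 44 (0.073 × 600).

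**6. Effect on an arm mean.** Take a deliberately extreme case: every EXE patient above 400 has the 46.7 mg/dl artefact of step 4, and no CON patient has any. The EXE mean change then shifts by 0.018 × 46.7 = 0.8 to 0.073 × 46.7 = 3.4 mg/dl. A realistic shift is smaller, because most such patients would not start at 800 and CON patients also receive lipid treatment.

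**The case against.** **A matter for the statistical analysis plan.** A validity limit for a derived laboratory value is often set there, and that plan was not available. This stands in part: a rule may exist. But the protocol does not merely omit a detail. It writes the derivation as a formula for all patients, and the formula can return impossible values.

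**The 400 mg/dl limit is not in the documents.** This stands. From the protocol alone, only zero or negative results are shown to be wrong. The figure of 400 is an assumed conventional value.

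**Entry.** A reader might infer that entry requires raised triglycerides. It does not: low HDL or specific treatment also meets the lipid trait.

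**Low values that may be real.** A reader might take any low calculated LDL beside a high total cholesterol as false. With TC 260, HDL 35 and TG 650 the result is 260 − 35 − 130 = 95. Non-HDL cholesterol of 225 does not refute this, because it includes the cholesterol in triglyceride-rich particles.

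**Change that is partly real.** With TC 240 and HDL 38, a TG fall from 500 to 250 raises calculated LDL from 102 to 152. It is tempting to call all 50 mg/dl error. But if non-HDL cholesterol stays at 202 while triglyceride-rich cholesterol falls, true LDL must rise. At k = 6 the true rise is 250/6 = 42 and the artefact 8. At k = 8 they are 31 and 19. With k moving from 8 to 6 the true rise is 500/8 − 250/6 = 21 and the artefact 29.

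**Arm bias is conditional.** Both arms share the formula and the central laboratory, so bias needs a different triglyceride change by arm. The protocol also treats lipids in everyone ("This program will eventually include glucose-, lipid- and BP-lowering agents as needed"), which should reduce the number of extreme values at 12 months. Both points stand and limit the size.

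**Conclusion.** The point holds as a minor one. The protocol fixes a formula with no limit, and at very high triglycerides it produces zero or negative LDL that counts as success and enters the change analysis. That much is arithmetic on the protocol's own definition.

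Everything about size rests on assumptions. The share above 400 mg/dl is about 2–7% under the assumed distributions. That share is not the number whose target status changes, which also requires true LDL at or above 100 and calculated LDL below it. Even the extreme case moves an arm mean by only about 1–3 mg/dl. Any between-arm bias needs a larger triglyceride fall in EXE and would then work against EXE.

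A reader might go on to infer that the trial's main conclusion is at risk. The documents do not support that: the HbA1c comparison and the sample size do not use LDL. Only secondary outcomes are affected, together with one covariate in the predictor regression.

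**What to change.** Make three changes, none of which touches eligibility or treatment:

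1. In Table 3, state in advance a triglyceride level above which calculated LDL is not relied on. The sponsor should choose and justify it; 400 mg/dl is offered only as an assumed conventional value.
2. Report change in non-HDL cholesterol (total minus HDL, both already measured centrally) for all randomised patients as the companion to LDL.
3. Report by arm how many LDL values exceed the limit at baseline and at end of study, and analyse LDL change and the LDL target both with and without them.

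The third item matters because simply dropping patients on end-of-study triglycerides conditions on something the intervention may change, and could remove more CON than EXE patients.

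The cost is wording and one derived variable, with no new samples or assays. The downside is that a few percent of LDL values are flagged as unreliable or missing, possibly unequally by arm. Non-HDL cholesterol still covers those patients. If the statistical analysis plan already has such a rule, a cross-reference in Table 3 would settle the limit; items 2 and 3 should then be checked against it.

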**Esercizi di mantenimento generale**

13 Ginnastica in casa 4.5

14 Ginnastica in palestra 6.0

15 Camminare velocemente 4.5

16 "Jogging" 6.0

17 Corsa 8-11 km/h 10.0

18 Corsa 12-16 km/h 15.0

19 Sollevamento pesi 6.0

**Attività acquatiche**

20 Sci acquatico 6.0

21 Surf 6.0

22 Navigazione a vela 3.0

23 Canotaggio o remi (dilettante) 3.5

24 Canotaggio o remi (professionista) 12.0

25 Fare un viaggio in canoa 4.0

26 Nuoto in piscina (piú di 150 metri) 6.0

27 Nuoto nel mare 6.0

28 Andare sott’acqua, snoorking 5.0

**Sport invernali**

29 Sci di discesa 7.0

30 Sci di fondo 8.0

31 Pattinaggio (ruote o ghiaccio) 7.0

**Altre attività**

32 Ippica 5.0

33 Boowling 3.0

34 Pallavolo 4.0

35 Ping-Pong 4.0

36 Tennis individuale 8.0

37 Tennis doppio 6.0

38 Badminton 7.0

39 Pallacanestro (non in partita) 6.0

40 Pallacanestro (giocando una partita) 8.0

41 Pallacanestro (da arbitro) 7.0

42 Squash 12.0

43 Calcio 10.0

44 Golf (portando il carrello) 3.5

45 Golf (camminando e portando le mazze) 5.5

46 Pallamano 10.0

47 Bocce 3.0

48 Arti marziali 10.0

49 Motociclismo 4.0

50 Ciclismo in strada o montagna 9.0

**Attività di giardinaggio**

51 Tagliare il prato con la falciatrice 4.5

52 Tagliare il prato manualmente 6.0

53 Pulire il giardino 4.5

54 Coltivare l’orto 5.0

55 Spalare la neve 6.0

**Lavori e attività casalinghe**

56 Lavoro di carpenteria in casa 3.0

57 Lavoro di carpenteria (all’aperto) 6.0

58 Imbiancare in casa 4.5

59 Imbiancare (all’aperto) 5.0

60 Pulire la casa 3.5

61 Spostare mobili 6.0

**Caccia e pesca**

62 Tiro con la pistola 2.5

63 Tiro con l’arco 3.5

64 Pesca in riva al mare 3.5

65 Pesca nel fiume (con gli stivali dentro l’acqua) 6.0

66 Caccia piccola 5.0

67 Caccia grossa (cervi, orsi...) 6.0

**Altro (specificare)**

68 .…………………………………………

69 .…………………………………………

70 .…………………………………………

**Table 5:** Progressive increase in global caloric expenditure per session.

| **1st month** | **3.0 Kcal/Kg BW** |
| --- | --- |
| **2nd month** | **3.1 Kcal/Kg BW** |
| **3thmonth** | **3.2 Kcal/Kg BW** |
| **4th month** | **3.3 Kcal/Kg BW** |
| **5th month** | **3.4 Kcal/Kg BW** |
| **6th month** | **3.5 Kcal/Kg BW** |
| **7th month** | **3.6 Kcal/Kg BW** |
| **8th month** | **3.7 Kcal/Kg BW** |
| **9th month** | **3.8 Kcal/Kg BW** |
| **10th month** | **3.9 Kcal/Kg BW** |
| **11th month** | **4.0 Kcal/Kg BW** |
| **12th month** | **4.1 Kcal/Kg BW** |

**Table 6:** Modified Balke protocol.

| **Step** | **Duration** | **Speed** | **Gradient** |
| --- | --- | --- | --- |
| 1 | 1 min. | 4,3 Km/h | 0 % |
| 2 | 1 min. | 4,3 Km/h | 2 % |
| 3 | 1 min. | 4,3 Km/h | 3 % |
| 4 | 1 min. | 4,3 Km/h | 4 % |
| 5 | 1 min. | 4,3 Km/h | 5 % |
| 6 | 1 min. | 4,3 Km/h | 6 % |
| 7 | 1 min. | 4,3 Km/h | 7 % |
| 8 | 1 min. | 4,3 Km/h | 8 % |
| 9 | 1 min. | 4,3 Km/h | 9 % |
| 10 | 1 min. | 4,3 Km/h | 10 % |
| 11 | 1 min. | 4,3 Km/h | 11 % |
| 12 | 1 min. | 4,3 Km/h | 12 % |
| 13 | 1 min. | 4,3 Km/h | 13 % |
| 14 | 1 min. | 4,3 Km/h | 14 % |
| 15 | 1 min. | 4,3 Km/h | 15 % |
| 16 | 1 min. | 4,3 Km/h | 16 % |
| 17 | 1 min. | 4,3 Km/h | 17 % |
| 18 | 1 min. | 4,3 Km/h | 18 % |

**Table 7:** ACSM’s equations for calculation of energy expenditure during aerobic exercise.

**Treadmill**

Walking speed: VO2 = [(speed(km/h)*1000 / 60*0,1)+(slope / 100*speed*1000 / 60*1,8)+3,5]

Running speed: VO2 = [(speed(km/h)*1000 / 60*0,2)+(slope / 100*speed*1000 / 60*1,8*0,5)+3,5]

**Ergometer**

Cycle: VO2 = [(power (watt) * 6,12 *1,8) / body weight (kg) +7]

Arm: VO2 = [(power (watt) * 6 * 3) / body weight (kg) + 3.5]

Elliptical: VO2 = A + B * power (watt) + C * power (watt)2 + D * power (watt) + E * power (watt) 2

body weight (kg) body weight (kg)

+ F * watt + G * power (watt)

body weight (kg)

*Coefficients:*

A =   3.5 ( basal  VO2)

B =    -0.05544

C =   +0.00024

D =   +7.06881

E =    -0.00612

F =    +0.29396

G =    -1.31488

**Step**

VO2 = 7 + 0.257 * SPM (steps per minute)
